### Outcome measurements

Patients will be required to complete the Chinese version of the Nepean Dyspepsia Index (NDI), which has been translated according to the validated long version of the Nepean Dyspepsia Index (NDI) [25]. The reliability and validity of this index were tested in the first phase of the ***973 program***. Patients will also be asked to complete the Symptom Index of Dyspepsia and the Mos 36-item Short Form Health Survey (SF-36). The Symptom Index of Dyspepsia focuses on four symptoms, namely postprandial distension, early satiety, epigastric pain and heartburn. Each symptom is then graded as asymptomatic (0 point), mild (1 point), moderate (2 points) or severe (3 points). The SF-36 is a Chinese version of an English test [2] to assess the quality of life.

The main outcome measurements in this trial will include differences in the Nepean Dyspepsia Index (NDI) and the Symptom Index of Dyspepsia, as measured before randomization, 2 weeks and 4 weeks after randomization, and 1 month and 3 months after the completion of treatment. Secondary outcome measures will include differences in the SF-36 before randomization, 4 weeks after randomization, and 1 month and 3 months after completing treatment.

### Patient safety

All patients will undergo two routine tests of blood, urine and stool samples, as well as electrocardiogram (ECG) examination, blood biochemical tests (ALT, AST, BUN, Scr), and blood glucose (BGlu) tests before randomization and immediately after completing treatment. These tests will help identify and exclude patients with serious illnesses of the heart, liver and kidney or other severe disease. Furthermore, the results of these tests will allow the assessment of risks associated with acupuncture and itopride treatments.

Adverse events caused by acupuncture or itopride, as well as the remedies for these events, will be documented during the treatment and follow-up phases. Such adverse events may include bleeding, hematoma, fainting, serious pain and local infection.

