**Participants safety**						
Laboratory test		X		X		
Adverse events		X	X	X	X	X

a. NDI = Nepean Dyspepsia Index; SID = Symptom Index of Dyspepsia; SF-36 = Mos 36-item Short Form Health Survey

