### Blinding

As the acupuncturists are responsible for sending randomization information and receiving notices of group assignments, it would not be practical to blind the acupuncturists to treatment allocations and patients' symptoms. Additionally, it is not possible to prevent patients from knowing if they have received acupuncture or itopride treatment. However, it is feasible and ethical to blind patients to the type of acupuncture they receive. In addition, we intend to conceal the group assignments from outcome assessors and our statistician. To assist with the blinding procedure, we named the groups A, B, C, D, E, and F in the medical records and case report forms (CRFs). The specific acupoints (or non-acupoints) will not be mentioned in these forms.

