We choose itopride as the drug control because it has been shown to be an effective drug for FD. Furthermore, itopride caused fewer adverse events than did other gastrointestinal prokinetic agents [21]. Therefore, we will attempt to maintain a non-inferiority design because acupuncture is associated with no significant side effects. However, our trial will be limited by our inability to blind patients from knowing whether they are receiving acupuncture or itopride treatment. This factor may cause a high drop-out rate in the itopride group because patients will expect to receive acupuncture treatment when they join the trial. To prevent the expected high drop-out rate, patients in the itopride group will be provided with 10 sessions of free acupuncture after the entire trial has been completed.

Central randomization, a strict and complete form of randomization, will be used in this trial. This method not only provides rapid determination of group assignment, but also ensures adequate allocation concealment. In this trial, we will use transcutaneous electric acupoint stimulation (HANS) to avoid the performance bias generated by acupuncture practitioners. This method will provide accurate electric stimulation to ensure that every patient receives the same level of treatment.

We have devoted much effort to defining the non-acupoint control groups because the locations of non-acupoint treatments will differ from those described in the literature. Most Chinese studies have selected non-acupoints that lie beside the therapeutic acupoint, and halfway between the two lines or two acupoints [24]. However, reports in the Western literature have recorded the location of non-acupoints differently [29,30]. In our previous trial, we designed our two control groups according to the consensus of a panel of acupuncture experts. Thus, the non-acupoint control group in the current study was defined according to the first phase of our ***973 program***.

Briefly, this trial aims to determine if acupuncture is an effective treatment for FD. We will also assess differences in the specific effects of acupoints, as described in traditional theories. Certain procedures described herein, such as the randomization procedure, as controlled by central randomization system, and the standardized protocol for acupuncture manipulation, can be applied to future acupuncture studies.

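### Patient safety words adverse-event recording by cause while Table 1 does not; if the causal wording governs, recorded clinical events depend on a prior judgement that may be unblinded

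*Protocol article*

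**What the plan says.** The Patient safety section of the protocol article holds the only prose rule on capturing adverse events: "Adverse events caused by acupuncture or itopride, as well as the remedies for these events, will be documented during the treatment and follow-up phases". It then gives examples: "Such adverse events may include bleeding, hematoma, fainting, serious pain and local infection".

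Table 1 has a row labelled "Adverse events" under participant safety. It is marked at week 0, week 2, week 4, and 1 and 3 months after treatment, with no reference to cause.

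Patient safety also requires blood, urine and stool tests, ECG, biochemistry and glucose in all patients before randomization and after treatment, and says that "the results of these tests will allow the assessment of risks associated with acupuncture and itopride treatments".

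On who knows the allocation, the Blinding section says of the treating staff that "it would not be practical to blind the acupuncturists to treatment allocations", and of patients that "it is not possible to prevent patients from knowing if they have received acupuncture or itopride treatment". Quality control says that acupuncturists are trained to complete the paper and electronic case report forms, and that blinded assessors carry out the outcome assessment. Neither section says who records adverse events or who judges their cause.

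The Discussion supports a non-inferiority approach against itopride on the ground that "acupuncture is associated with no significant side effects".

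**The concern.** Read as written, the Patient safety sentence makes causation part of what qualifies for documentation, so the judgement of cause comes before the record instead of being a field within it. An event that nobody attributes to treatment could then go unrecorded, and no later analysis can recover it. Unexpected harms are the ones least likely to be attributed.

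The risk is greatest for acupuncture against itopride. For that contrast neither the acupuncturist nor the patient is blind, and the examples listed are all of a needling type. The Background lists nausea and vomiting among the features of functional dyspepsia itself, so whether such a complaint is put down to the disease or to treatment is a matter of discretion. If that discretion is exercised differently between arms, the recorded rates can differ when the true risks do not, or agree when they do not. At stake is the description of clinical harms by arm. The efficacy analysis is not touched.

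**Working it through.** No figure in the protocol article bears on this point, so there is none to reproduce. The check is a comparison of the text, followed by an illustration on assumed rates.

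**Text comparison**

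| Question | Patient safety | Table 1 | Other sections |
|---|---|---|---|
| Which clinical events are documented? | Those caused by acupuncture or itopride | Adverse events, no qualifier | – |
| When? | Treatment and follow-up phases | Five visits | – |
| Examples? | Five, all needling-type; the wording makes the list illustrative | None | – |
| Who records and who judges cause? | Not stated | Not stated | Acupuncturists are trained to complete the forms; blinded assessors handle outcome assessment (Quality control) |
| Who knows the arm? | – | – | Acupuncturists, for all six arms; patients, for acupuncture versus itopride (Blinding) |
| Safety data needing no attribution? | Laboratory tests and ECG, all patients | Laboratory tests at week 0 and week 4 | – |

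The two places differ on which events count. Table 1 mainly fixes timing, and the Patient safety sentence is the one that describes content. A row label does not clearly override it, so a site following the prose could reasonably record attributed events only.

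**Illustration**

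Inputs: n = 120 per arm (Abstract and Table 1). Assumed, with no source in the documents: the same true risk p of an adverse event in two arms; a share a₁ = 0.9 of events attributed, and so recorded, in one arm; a share a₂ = 0.7, 0.5 or 0.3 in the other.

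Recorded rates: r₁ = p·a₁ and r₂ = p·a₂. With r̄ = (r₁ + r₂)/2, the approximate chance that a two-sided 5% test declares a difference is

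Φ{ [ |r₁ − r₂| − 1.96·√(2r̄(1 − r̄)/n) ] / √( [r₁(1 − r₁) + r₂(1 − r₂)]/n ) }.

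Worked case, p = 0.20 and a₂ = 0.5:
- r₁ = 0.20 × 0.9 = 0.18; r₂ = 0.20 × 0.5 = 0.10; r̄ = 0.14.
- Null standard error: √(2 × 0.14 × 0.86/120) = 0.0448.
- Alternative standard error: √((0.1476 + 0.0900)/120) = 0.0445.
- (0.08 − 1.96 × 0.0448)/0.0445 = −0.175, and Φ(−0.175) ≈ 0.43.

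All cases (recorded rates, then the chance of a falsely significant difference):

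| True risk, both arms | 90% v 70% attributed | 90% v 50% | 90% v 30% |
|---|---|---|---|
| 10% | 9% v 7%: 8% | 9% v 5%: 23% | 9% v 3%: 50% |
| 20% | 18% v 14%: 13% | 18% v 10%: 43% | 18% v 6%: 82% |
| 30% | 27% v 21%: 19% | 27% v 15%: 63% | 27% v 9%: 96% |

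The nominal figure is 5% throughout. Loss occurs even when attribution is equal: at a 10% risk, 120 × 0.10 = 12 patients with an event are expected in an arm, and at 50% attribution 6 of them are never recorded.

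**The case against.** The strongest reply is that the sentence says treatment-caused events will be documented, not that others will be left out, and that Table 1 schedules adverse events without restriction. That stands as far as it goes: a reader might infer that only attributed events are kept, but the article does not say so. What remains is that two places differ and that the only prose on content is the causal one.

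A reader might also infer that unblinded acupuncturists do the filtering. The documents do not establish this. They know the allocation and are trained to complete the forms, which makes it plausible, but the person who assesses causality is not named and blinded assessors exist. A journal article may leave that assignment to the full protocol, so its absence is not counted as a fault here.

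It is also tempting to say that the whole safety comparison is compromised. It is not, because laboratory tests and ECG are done in all patients regardless of attribution. Nor do the examples show that the forms prompt only for needling events: the list is open-ended, the sentence before it names itopride, and fainting or serious pain is not peculiar to needling.

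Finally, the declared outcomes are the two dyspepsia indices and the SF-36, the stated hypotheses concern primary outcomes only, and the Discussion uses acupuncture's safety as a prior reason for the design. No formal between-arm test of adverse events is described. This limits the consequence to the safety reporting. It does not remove it, since Patient safety itself sets out to assess the risks of both treatments.

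**Conclusion.** The point holds in conditional form. Patient safety defines documented adverse events by cause and Table 1 does not. If the Patient safety wording governs, recording of clinical events depends on a prior causality judgement that unblinded staff may make. That can bias the acupuncture-versus-itopride comparison of clinical events and let unexpected harms in any arm go unrecorded.

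Its size in this trial is unknown. The illustrated chances of a false difference, from 8% to 96%, rest entirely on assumed event risks and attribution shares. They show that distortion is possible, not that it will occur. The correction is worth making before recruitment because events that were not recorded cannot be recovered afterwards.

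**What to change.** Align the Patient safety sentence with Table 1:

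- Record all adverse events, regardless of presumed cause, in all six arms at the Table 1 visits, elicited with the same open question in every arm.
- Record relatedness as a separate field after the event is entered, judged where feasible by one of the blinded assessors already on the team.
- Report all events and related events by arm.
- If examples are kept, state that they do not limit what is recorded.

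The cost is a change to the safety wording and the adverse-event page of the case report form, and slightly more data entry. No new visits or staff are needed. Blinded grading will not always be possible, because the description of an event can reveal whether needles or a drug were used.

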### Quality control

All acupuncturists are required to undergo special training, including theoretical and practical lessons, before participating in the trial. All researchers and clinicians must understand the purpose and design of this trial, as well as treatment strategies and measures of quality. In addition, acupuncturists will be trained to use the central randomization method, complete the CRFs and electro-CRFs, locate the points and manipulate the needles. Acupuncturists who have completed the required training and have passed an examination will be considered qualified to assist with this trial. Several trained outcome assessors, who are blinded to group assignment, will be responsible for the outcome assessment. Additionally, to maintain accuracy and quality throughout our clinical study, audits will be conducted on CRF completion and compliance with standard operation procedures (SOPs). Finally, quality control and assurance will be presented in written form by trained monitors at every participating hospital once a month. Patient compliance and voluntary withdrawal from the study (including the reason for withdrawal) will be fully documented.

### Statistical analysis

Sample size was determined prospectively as described in a previous study that used similar outcome measurements [21]. The following formula was used to estimate sample size [26]:

A previous study reported [21] an improvement of 18.0 in the main outcome NDI index score after treatment with 50 mg itopride. In this study, we anticipate an improvement of no less than 15.0 after acupuncture treatment; however, there are no previous data regarding NDI scores for the treatment of FD using acupuncture. Accordingly, an improvement of 3.0 in the NDI scores of two groups will be considered minimally significant. Standard deviation was defined as 22.0, according to the previous study [21]. Calculations were performed using 90% power and a 5% significance level, resulting in an estimated 120 patients per group. Thus, we must enroll 720 patients in the six groups, to allow for a 15% withdrawal rate.

The two-sided null hypotheses to be tested include:

(1) The primary outcomes of the acupoint treatment groups will be equivalent to those of the itopride control group.

(2) The primary outcomes of the acupoint treatment groups will be equivalent to those of the non-acupoint control group.

(3) The primary outcomes of the acupoint treatment groups will be equivalent to each other.

We will test these hypotheses with a significance level of P < 0.05. The first step of the analysis will involve comparing the baseline characteristics of the groups. The second step will be to compare the efficacy of acupoint and itopride in the treatment of FD. The third step will involve comparing the acupoint treatment group with the non-acupoint control group. If acupoint treatment is more effective than non-acupoint treatment in the treatment of FD, the fourth step will involve comparing the efficacy of four acupoint treatments.

The analyses of baseline characteristics, as well as the primary, secondary and other outcomes, are based on the intention-to-treat (ITT) principle. Data distribution is expected to be normal owing to the large sample size. However, any skewed distribution data will be transformed prior to analysis. The repeated measures analysis will be used in the assessment of different time points (such as comparing NDI scores before randomization, 2 weeks and 4 weeks after randomization, and 1 month and 3 months after the completion of treatment). Missing values will be addressed using the method of last observation carried forward (LOCF) and multiple-imputation. We will perform sensitivity analysis to determine how these two methods affect the analytic results. General linear mixed models, adjusted for clinical site, will be used to study the effects of treatments on outcomes from baseline to 3 months. Additionally, time-to-event outcomes between groups will be compared using the log-rank test.

Analysis of data will be performed in a blinded manner by a designated statistician at the National Clinical Trial Center of Chinese Medicine (Chengdu GCP Center) in China. Statistical analyses will be performed using SPSS 15.0 statistics software (SPSS Inc, Chicago, Illinois, USA) and SAS 9.0 (SAS Institute Inc., Cary, North Carolina, USA).

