## Background

Functional dyspepsia (FD) is defined as chronic upper abdominal discomfort or pain, heartburn, early satiety, nausea, vomiting, abdominal distension and bloating, without any apparent organic, systemic, or metabolic pathology to explain these symptoms [1-3]. An epidemiological survey of Western countries showed that the prevalence of FD ranges from 11.5% to 14.7% [4]. An additional study conducted in Tianjin, China, revealed that 23.29% of the population suffers from FD [5]. A common and well-recognized public health problem, FD reduces patient quality of life and increases the economic burden of medical care [6-11].

Although several classes of drugs (such as proton pump inhibitors, H2-blockers, and prokinetic drugs) have been used in clinical practice and some (such as antisecretory agents or prokinetics) have been effective in placebo-controlled trials, only a small proportion of patients report sufficient relief from these treatments [12].

The exact etiology of FD remains unclear; thus, it is not surprising that current treatments for FD are of limited efficacy and that alternative therapies, including acupuncture, are attractive to both patients and practitioners [13]. Acupuncture has been used in China for many years to treat gastrointestinal symptoms, including acute and chronic gastroenteritis, diarrhea, constipation and gastroduodenal ulcers [14]. Several randomized controlled trials (RCTs) have suggested that acupuncture is an effective treatment for FD, particularly with regards to dyspeptic symptoms, belching and anorexia [15-17]. However, it has been difficult to draw firm conclusions from the results of these RCTS due to the poor quality of the studies and the small sample sizes. Therefore, the mechanisms by which acupuncture treat FD, or whether this therapy works at all, remain the subject of debate. Therefore, we have designed a multicenter randomized controlled trial to address these problems and provide more conclusive data on the use of acupuncture to treat FD.

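### The only threshold available for a non-inferiority reading against itopride, 3.0 NDI points, is the gap between two within-arm improvements and is not tied to itopride's effect over placebo

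*Protocol article*

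**What the plan says.** The Statistical analysis section of the protocol article builds its threshold in three steps.

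- Itopride, from the cited earlier study: "A previous study reported [21] an improvement of 18.0 in the main outcome NDI index score after treatment with 50 mg itopride".
- Acupuncture, by assumption: "we anticipate an improvement of no less than 15.0 after acupuncture treatment". The article adds that "there are no previous data regarding NDI scores for the treatment of FD using acupuncture".
- The result: "Accordingly, an improvement of 3.0 in the NDI scores of two groups will be considered minimally significant".

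The section then lists three two-sided null hypotheses on the primary outcomes: acupoint groups against itopride, acupoint groups against non-acupoint, and the acupoint groups against each other. They are worded as equivalence but are to be tested at the 5% level, so they work as nulls of no difference. In the stepwise plan the itopride comparison is step 2 and the non-acupoint comparison is step 3. Only step 4, among the acupoint groups, depends on an earlier result.

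The Discussion, speaking of itopride as the drug control, says "we will attempt to maintain a non-inferiority design". The Control groups section calls itopride effective, citing the same earlier study, but gives no effect over placebo.

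**The concern.** A non-inferiority conclusion against an active drug is indirect evidence of efficacy. It works only if the margin is smaller than the drug's own advantage over placebo. A change from before to after treatment in one arm also contains placebo response, natural course and regression to the mean. The gap between two such changes says nothing about how much of the 18.0 is due to the drug, and here one of the two is assumed without data.

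The article names a non-inferiority aim in one place and one numerical threshold in another, and offers no other margin. A reader who joins the two will take 3.0 as the margin. A reader who follows the listed hypotheses may instead take a non-significant difference from itopride as a favourable result. Either reading bears on the trial's first aim, whether acupuncture is effective in functional dyspepsia, and neither is anchored to placebo.

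**Working it through.** **Origin of the threshold.** 18.0 − 15.0 = 3.0, so the article's figure is reproduced.

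**Margin or difference?** The sample-size arithmetic does not settle which was meant. With SD 22.0 and 90% power:

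- Difference of 3.0, two-sided 5%: n = 2 × [22 × (1.960 + 1.282) / 3]² ≈ 1131 per group.
- Margin of 3.0, no true difference, one-sided 2.5%: the same formula, again 1131.

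Neither gives the stated 120 per group. That is a separate problem, used here only because it fixes the precision at the planned size.

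**Share of the drug effect preserved.** Let E be itopride's true NDI advantage over placebo. E is not in the document; the values are assumptions. Share preserved by a margin of 3.0 = 1 − 3/E.

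| Assumed E | Share preserved |
|---|---|
| 2 | −50% |
| 3 | 0% |
| 4 | 25% |
| 6 | 50% |
| 8 | 62.5% |
| 10 | 70% |

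Half is kept only if E is at least 6, that is, if placebo patients would have improved by 18.0 − 6.0 = 12.0 or less.

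**How often a placebo-like arm would look acceptable.** Compare one acupoint group with itopride, 120 each, SD 22.0. SE = 22 × √(2/120) = 2.84. Suppose the acupoint arm is truly no better than placebo, so it falls E short of itopride.

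- Confidence-interval rule (95% limit excludes a deficit of 3.0): Φ((3 − E)/SE − 1.96)
- Point-estimate rule (observed deficit below 3.0): Φ((3 − E)/SE)
- Non-significant two-sided test: Φ(1.96 − E/SE) − Φ(−1.96 − E/SE)

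| Assumed E | CI rule | Point estimate | Non-significant |
|---|---|---|---|
| 0 | 18% | 85% | 95% |
| 2 | 5% | 64% | 89% |
| 3 | 2.5% | 50% | 82% |
| 6 | 0.1% | 15% | 44% |
| 9 | under 0.1% | 2% | 11% |

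At E = 0 placebo and itopride are the same, so the first row also describes an arm truly equal to itopride: at 120 per group it would meet the CI rule only 18% of the time. At about 1131 per group, the CI rule would pass a placebo-like arm 90% of the time at E = 0, 58% at E = 1, 19% at E = 2 and 2.5% at E = 3.

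**Internal check on itopride.** None of the three hypotheses sets itopride against the non-acupoint arm, so the plan as listed does not test whether itopride worked in this trial.

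**The case against.** The strongest reply is that the article sets no non-inferiority margin. The 3.0 is an input to the sample size, the tests are two-sided, and the non-inferiority wording is one tentative sentence in the Discussion. This stands: 3.0 as a margin is an inference from joining two sections. What remains is that the sections do not agree, and that no other threshold is available to anyone who takes the Discussion at its word.

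Second, the document gives some ground for believing that itopride works. The Background says of drug treatment that "only a small proportion of patients report sufficient relief from these treatments", but the same sentence says that some classes, prokinetics among them, have beaten placebo, and the Discussion places itopride among the prokinetics. This also stands. It supports E above zero but not any particular size, and the remark on limited relief concerns several drug classes, not itopride on the NDI.

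Third, the trial has a non-acupoint arm of 120, compared with the acupoint groups in step 3. That is a real safeguard for the overall efficacy conclusion, but a partial one. Step 2 does not wait for step 3. The arm receives needling and electro-stimulation, and patients know whether they are on needles or drug, so it does not stand in for a drug placebo.

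Fourth, under a strict confidence-interval rule at 120 per group the risk is small, as the table shows. This stands for that rule. The article states no such rule, and the risk is much larger if success is read from a point estimate or from non-significance.

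A reader might infer that 3.0 is the trial's declared margin and that an arm no better than placebo would meet it, so that the itopride comparison carries no evidence at all. The documents do not support that: they never label 3.0 a margin, and they do not give E.

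**Conclusion.** The point holds in a limited form. The non-inferiority aim and the tests of equality are not reconciled, and the one threshold given cannot support a non-inferiority conclusion on the basis stated for it. Its size depends on E: the threshold is as large as the whole drug effect or larger if E is 3 or less, and keeps at least half of it if E is 6 or more. The document does not say where E lies.

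The conclusion rests on reading 18.0 as a before-to-after change, its natural sense beside the 15.0 that is subtracted from it. If 18.0 were already net of placebo, a margin of 3.0 would keep 1 − 3/18 = 83%, and the criticism of the size of the threshold would fall away; the mismatch between the sections would remain. The pass rates also assume SD 22.0, normal estimates and one acupoint group of 120 against itopride.

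This affects one of the three planned comparisons, but one that bears on the first aim. It should be corrected; it does not invalidate the trial.

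**What to change.** Reconcile the Statistical analysis section with the Discussion, so that both say whether the itopride comparison is a test of difference or of non-inferiority.

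Do not use 3.0 as a non-inferiority margin unless it is shown to be smaller than itopride's placebo-controlled NDI effect, for example from the study already cited if it gives one. Otherwise:

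- drop the non-inferiority reading;
- report acupoint minus itopride as a difference with its 95% confidence interval, without treating non-significance as similarity;
- rest the efficacy conclusion on acupoint versus non-acupoint.

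The second route needs only rewording, and its price is that the non-inferiority claim may be given up. The first route can cost more. What share of the effect a margin should preserve is a matter of convention. If half is chosen, for illustration, E = 4 gives a margin of 2 and about 2543 per group before dropout, and E = 10 gives a margin of 5 and about 407 (SD 22.0, one-sided 2.5%, 90% power). Both are well above 120.

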### Randomization

A central-randomization scheme will be performed at the Chengdu Good Clinical Practice (GCP) Center, which is affiliated with the National Clinical Trial Center of Chinese Medicine. This scheme will be used to assign patients to one of six groups in a 1:1:1:1:1:1 ratio. A permuted-block randomization procedure, which is automatically under the control of a central computer system, will be used to generate an allocation sequence and blind researchers to the group assignments. Patients who meet the inclusion criteria will be referred to acupuncturists at one of the eight study hospitals. The cell phones of all acupuncturists will be approved and assigned specific ID numbers after the acupuncturist completes a special training course designed for this trial. The acupuncturists will then use the registered cell phones to send randomization information to the GCP Center. This randomization information will include the subject's name in a pinyin format, the subject's numerical birthday and the subject's gender. Once the GCP Center computer system receives the randomization information, it will randomly assign patients to an acupoint treatment group or to the control group. Random numbers and group assignments will be sent from the GCP Center to the acupuncturists via e-mail or short message service (SMS). This procedure will ensure adequate randomization concealment. Patients will be blinded to the type of acupuncture treatment they receive.

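### The 120 patients per group do not follow from the stated inputs: power for a 3.0-point NDI difference is about 16–18%, not 90%, and the 15% withdrawal allowance cannot be traced

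*Protocol article*

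**What the plan says.** All the sample-size inputs are in the Statistical analysis section of the protocol article. An earlier itopride study is cited for "an improvement of 18.0 in the main outcome NDI index score after treatment with 50 mg itopride". For acupuncture, "we anticipate an improvement of no less than 15.0 after acupuncture treatment". From these the section concludes that "an improvement of 3.0 in the NDI scores of two groups will be considered minimally significant". The SD is set at 22.0 from the same earlier study. The result follows: "Calculations were performed using 90% power and a 5% significance level, resulting in an estimated 120 patients per group". The next sentence gives the total: "Thus, we must enroll 720 patients in the six groups, to allow for a 15% withdrawal rate".

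The tests are introduced as two-sided: "The two-sided null hypotheses to be tested include". They cover acupoint arms against itopride, against non-acupoints, and against each other. Allocation is equal across the six arms (Randomization section), and the abstract and Table 1 also give 120 per arm. The Discussion separately says that a non-inferiority design will be attempted against itopride, without naming a margin.

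**The concern.** A difference of 3.0 against an SD of 22.0 is a standardised difference of 3.0/22.0 = 0.14. Detecting an effect that small with 90% power takes far more than 120 patients per arm. The total is also hard to follow: it is said to allow for 15% withdrawal, yet it is six times the number presented as the output of the power calculation.

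The trial asks whether acupuncture works and whether acupoints differ, and the acupoint arms are compared with each other only if acupoint treatment first proves better than non-acupoint treatment. If power for the protocol's own smallest relevant difference is low, a non-significant result is likely even when that difference is real. A reader who trusts the 90% would give such a result too much weight.

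**Working it through.** **Inputs (Statistical analysis section).** Difference d = 18.0 − 15.0 = 3.0; SD = 22.0; power 90%; significance 5%, two-sided; stated result 120 per group; withdrawal 15%; total 720.

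**Step 1: try to reproduce 120.** For two equal groups:

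n = 2 × (1.960 + 1.282)² × 22.0² / 3.0² = 1,130.1, so 1,131 per group.

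This is about 9.4 times the stated number. Dividing by 0.85 for withdrawal gives 1,331 per group, or 7,986 in six groups. Other set-ups with the same difference and the figure 22.0 do not give 120 either, nor about 102 before inflation:

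| Set-up | n per group |
|---|---|
| One-sided 5%, 90% power | 922 |
| Two-sided 5%, 80% power | 845 |
| One-sided 5%, 80% power | 665 |
| Non-inferiority, margin 3.0, true difference 0, 90% power, one-sided 2.5% / 5% | 1,131 / 922 |
| One-sample, 90% power, two-sided / one-sided | 566 / 461 |
| Four acupoint arms pooled against one control, two-sided, 90% power | 707 controls |
| Six-arm analysis of variance, one arm 3.0 apart, 90% power | 1,064 |
| Baseline-adjusted, assumed correlation 0.5 / 0.7, two-sided, 90% power | 848 / 577 |
| 22.0 misread as a variance | 52 |

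For 120 to be right (two-sided, 90% power), the SD would have to be about 7.2. With SD 22.0, a baseline correlation of about 0.95 would be needed.

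**Step 2: power for 3.0 points, unadjusted comparison of two arms, two-sided 5%.**

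- 120 analysed per group: SE = 22.0 × √(2/120) = 2.84; 3.0/2.84 − 1.960 = −0.90; power about 18%.
- 102 analysed per group: SE = 22.0 × √(2/102) = 3.08; 3.0/3.08 − 1.960 = −0.99; power about 16%.
- Four acupoint arms pooled against one control: 480 versus 120 gives about 27%; 408 versus 102 gives about 23%.
- One-sided 5%, two arms: about 28% (120) or 25% (102).

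**Step 3: what the trial can detect with two arms, two-sided.**

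- 90% power: 3.242 × SE = 9.2 points (120) or 10.0 points (102).
- 80% power: (1.960 + 0.842) × SE = 8.0 points (120) or 8.6 points (102).
- 95% CI half-width: 1.960 × SE = 5.6 points (120) or 6.0 points (102).

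**Step 4: the withdrawal allowance.** 6 × 120 = 720.

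- If 120 is the calculated number, nothing has been added. An allowance of 15% would need 120/0.85 = 141.2, so 142 per group and 852 in total.
- If 120 already includes the allowance, 120 × 0.85 = 102 per group are evaluable, and power for 3.0 is about 16%.

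**The case against.** **The formula is not visible.** The sample-size formula did not survive in the text available here. The supportable statement is therefore that no standard formula tried gives 120, not that none could. This does not rescue the figure, because every input is printed.

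**The planned analysis is not a plain two-arm test.** The protocol plans repeated measures and mixed models adjusted for site, by intention to treat with imputation, so 102 is not the planned analysis set. The acupoint arms may also be pooled in the comparisons with itopride and non-acupoints. This stands, and the 16–18% must carry its assumptions. Even so, baseline adjustment at an assumed correlation of 0.5 to 0.7 gives only about 23–32% for two arms of 120. Combined with pooling (480 versus 120), it gives about 34–46%. None of these is near 90%.

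**A reader might infer that 720 contains no withdrawal allowance at all.** The documents do not support that. Since 102/0.85 is exactly 120, the 120 may already be inflated. What can be said is that the text does not show which reading applies.

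**A reader might infer that the non-acupoint and between-acupoint contrasts were never sized.** That is also too strong. The 3.0 is stated for two groups without naming them, and with equal arms and one SD a pairwise calculation covers every pair. What stands is that 3.0 is derived only from 18.0 versus 15.0, with no separate rationale for the contrasts that carry the specificity question.

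**A reader might infer that every detectable difference exceeds half of itopride's 18.0.** That holds at 90% power (9.2/18.0 = 51%; 10.0/18.0 = 56%) but not at 80% power (8.0/18.0 = 44%; 8.6/18.0 = 48%).

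**The document does not say it will read non-significance as no difference.** That is correct. The misreading is a risk created by the 90% claim, not a stated plan.

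**Conclusion.** The concern holds in this form and must be corrected. The stated 120 per group contradicts its own inputs by a factor of about 9.4 (two-sided) or 7.7 (one-sided, 922/120). Power for the protocol's own 3.0-point difference is about 16–18%, not 90%. That range assumes SD 22.0, a two-sided 5% test, an unadjusted comparison of two arms, and 102 to 120 analysed per arm. Pooling or plausible baseline adjustment raises it without approaching 90%.

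The conclusion does not depend on how the withdrawal sentence is read: one reading leaves no allowance, and the other leaves 102 evaluable per arm. Nor does it depend on whether 3.0 is a superiority difference or a non-inferiority margin. As a margin with no true difference, power is about 16–18% at one-sided 2.5% and 25–28% at one-sided 5%.

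**What to change.** Keep 720 and reword the sample-size paragraph:

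1. Withdraw the claim of 90% power for 3.0 points.
2. State that, at SD 22.0 and for an unadjusted comparison of two arms, the trial has 90% power for about 9.2 points (120 analysed) or 10.0 points (102 analysed), 80% power for about 8.0 or 8.6 points, and about 16–18% power for 3.0.
3. State whether 120 is before or after the 15% withdrawal.
4. Say whether 3.0 is a superiority difference or the margin for the non-inferiority design mentioned in the Discussion, and whether it is meant for the non-acupoint and between-acupoint contrasts as well.
5. Report pairwise differences with 95% CIs (half-width about 5.6 to 6.0 points), and do not take a non-significant result as evidence against a 3-point difference.

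The cost is a rewritten paragraph and a less favourable power statement. No extra patients and no change to the arms or visits are needed.
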